**Statement of Compliance**

1. [The trial will be carried out in accordance with International Conference on Harmonization Good Clinical Practice (ICH GCP) and the following:

- United States (US) Code of Federal Regulations (CFR) applicable to clinical studies (45 CFR Part 46, 21 CFR Part 50, 21 CFR Part 56, 21 CFR Part 312, and/or 21 CFR Part 812)

National Institutes of Health (NIH)-funded investigators and clinical trial site staff who are responsible for the conduct, management, or oversight of NIH-funded clinical trials have completed Human Subjects Protection and ICH GCP Training.

The protocol, informed consent form(s), recruitment materials, and all participant materials will be submitted to the Institutional Review Board (IRB) for review and approval. Approval of both the protocol and the consent form must be obtained before any participant is enrolled. Any amendment to the protocol will require review and approval by the IRB before the changes are implemented to the study. In addition, all changes to the consent form will be IRB-approved; a determination will be made regarding whether a new consent needs to be obtained from participants who provided consent, using a previously approved consent form.

# List of Abbreviations

| **AE** | Adverse Event |
| --- | --- |
| **CFR** | Code of Federal Regulations |
| **CRF** | Case Report Form |
| **CTSC** | Clinical Translational Science Center |
| **DSMB** | Data Safety Monitoring Board |
| **DSMP** | Data Safety Monitoring Plan |
| **FDA** | Food and Drug Administration |
| **GCP** | Good Clinical Practice |
| **HIPAA** | Health Insurance Portability and Accountability Act of 1996 |
| **HRBFA** | Human Research Billing Analysis Form |
| **HUD** | Humanitarian Use Device |
| **ICF** | Informed Consent Form |
| **IDE** | Investigational Device Exemption |
| **IND** | Investigational New Drug |
| **IRB** | Institutional Review Board |
| **PHI** | Protected Health Information |
| **PI** | Principal Investigator |
| **REDCap** | Research Electronic Data Capture |
| **SAE**  **SNM** | Serious Adverse Event  Social Network Member |
| **SUSAR** | Suspected Unexpected Serious Adverse Reaction |
| **UIRTSO** | Unanticipated Problem Involving Risks to Subjects or Others |
| **WCM** | Weill Cornell Medicine |

# 1. Protocol Summary

Full Title: Reducing OBesity Using Social Ties (ROBUST): Randomized Controlled Trial Short Title: ROBUST- RCT

Clinical Phase: III

Principal Investigator: [name], MS

**Study Description:** Randomized controlled trial comparing two behavioral weight-loss interventions; a social-network enhanced lifestyle intervention (Intervention group) and an individual level lifestyle intervention (Control group), among Black and Hispanic adults with obesity over the course of 24 weeks. This study aims to test the feasibility and acceptability reforming interpersonal barriers and addressing social network barriers to behavior change, by engaging social network members in a lifestyle intervention for weight loss compared to the lifestyle intervention alone.

**Sample Size:** *N=* *66 (Intervention index participants)*

*N=132 (Intervention Social Network members)*

*N= 66 (Control participants)*

*N=264 (Total Sample Size)*

**Enrollment:** In the intervention group, this study will enroll 66 index participants and 132 social network member subjects. In the control group, this study will enroll up to 66 index participants.

**Study Population:** Individuals who self-identify as Non-Hispanic Black or Hispanic adults 18 years of age or older with a calculated BMI ≥ 30 kg/m2

**Enrollment Period:** *24 weeks*

**Study Design:** Randomized controlled trial comparing a social-network enhanced lifestyle (intervention group) to an individual-level lifestyle intervention (control group). Subjects in both arms (n=66 each) will receive the same number of behavioral coaching sessions (15 total) with four sessions conducted in person (baseline, week 8, week 16, and week 24), and the remaining 11 sessions conducted virtually. Subjects randomized to the social network intervention will nominate up to a maximum of two members of their social network (n=132) who will also be consented at baseline, complete a brief baseline interview, and attend the virtual coaching sessions with the randomized subject at weeks 3, 5, and 15. The social network members will also complete a close-out study interview at week 24.

**Description of Sites/**

**Facilities Enrolling**

**Participants:** Four sites including: Weill Cornell Internal Medicine Associates, Weill Cornell Urology locations in Manhattan & Brooklyn, and Weill Cornell Primary Care at Lower Manhattan. The study is not intended to include sites outside of the United States.

**Study Duration:** *3 years*

**Participant Duration:** 24 weeks (6 months)

**Study Agent/Device Name**

**Intervention Description:** The social-network enhanced lifestyle Intervention will target:

1. The relationship between participants and their social network members to induce a positive affect, social support, and collaborative problem solving (communal coping) through three communications skills training sessions.
2. Acquisition of behavioral skills that will enhance adherence to dietary and physical activity goals through one-on-one lifestyle coaching and dietary counseling sessions

**Primary Objectives:** Evaluate the feasibility of each participant in the ROBUST intervention engaging up to two personal social network members to participate in the study.

**Secondary Objectives:** Evaluate the impact of the ROBUST intervention on modifying the target social network barriers of: social undermining and unhealthy weight norms by activating a communal coping process within the personal network, and interpersonal conflicts by inducing positive affect to build resiliency.

Examine if positive changes in these social network processes result in greater adoption of healthier diets, increased physical activity, and weight loss at 24 weeks.

**Exploratory Objectives:** Examine the ROBUST Intervention’s effect on weight change and

related behaviors among network members who participate in the study.

Identify social network phenotypes that may be predictive of differential weight loss patterns.

**Primary Endpoints:** At least 75% attendance rate for the participant and their network members in their respective behavioral coaching sessions.

80% of participants or more to have at least one network member engage in the study.

85% of participants and their network members or more to complete the final study assessment.

**Secondary Endpoints:** Increase in positive communication and problem solving scores on the McMaster Family Assessment Device (FAD) for the participant and their social network members.

Decrease in social norms that promote unhealthy eating and physical inactivity (unhealthy weight norms).

Increase in participant physical activity and decrease in caloric intake

## 1.1 Schema

[figure not shown]

## 1.2 Study Objectives and End Points

### **1.2.1 Primary Objectives**

To evaluate the feasibility of each participant in the ROBUST intervention engaging up to two personal social network members to participate in the study.

### **1.2.2 Secondary Objectives**

To evaluate the impact of the ROBUST intervention on modifying the target social network barriers of social undermining and unhealthy weight norms by activating a communal coping process within the personal network, and interpersonal conflicts by inducing positive affect to build resiliency.

To examine if positive changes in these social network processes result in greater adoption of healthier diets, increased physical activity, and weight loss at 24 weeks.

### **1.2.3 Exploratory Objectives**

### To examine the ROBUST Intervention’s effect on weight change and related behaviors among social network members who participate in the study.

To identify social network phenotypes that may be predictive of differential weight loss patterns.

### **1.2.4 Primary Endpoints**

At least 75% attendance rate for the participant and their network members in their respective behavioral coaching sessions.

80% of participants or more to have at least one network member engage in the study.

85% of participants and their network members or more to complete the final study assessment.

### **1.2.5 Secondary Endpoints**

Increase in positive communication and problem solving scores on the McMaster Family Assessment Device (FAD) for the participant and their social network members.

Decrease in social norms that promote unhealthy eating and physical inactivity (unhealthy weight norms).

Increase in participant physical activity, and decrease in caloric intake.

# 2. Background

## 2.1 Scientific background of the problem

Eliminating the disproportionate burden of metabolic diseases has remained a pervasive objective for the United States healthcare system. It has become increasingly recognized that obesity is a constant factor of multiple chronic comorbidities, such as cardiovascular disease, Type 2-Diabetes (T2D), and certain forms of cancer among thousands of Americans. The Centers for Disease Control and Prevention (CDC) defines obesity as a “public health problem”.^1^ A study in New York city looking at the disproportionate rate differences in the prevalence of obesity among racial and ethnic groups highlights that racial minorities such as non-Hispanic Blacks (36.9%) and Hispanics (36.8%) are two times to have obesity and be subjected to other metabolic diseases then Asian/Pacific Islanders (16.5%) and 1.5 times more than non-Hispanic whites (27.9%).^2-4^

However, the explosive rise in the prevalence of obesity cannot be solely explained by individual factors alone. Researchers have recognized that social-environmental factors also contribute to obesity risk and inequities. Social influences in particular have a pervasive impact on obesity and related behaviors but are typically not addressed in interventions.^5,6-10^ Pilot studies focused on reducing negative social influences have been found to improve intervention effectiveness, address the obesity epidemic, and promote healthy behavior change by incorporating social network intervention strategies.^5,7,11^ This raises a critical need to develop efficacious and tailored approaches to reduce the prevalence of obesity across high-risk communities by addressing social influences on weight loss habits*.* ^9^

## 2.2 Behavioral Intervention to be tested

An innovative way to target social influence as a path to reduce the prevalence of obesity is through Social Network Interventions.^12,13, 23,24^ Social Network interventions are an intentional effort to modify or use the characteristics of social networks to improve, generate, and maintain healthy behaviors among individuals and populations. Researchers have leveraged social network intervention strategies, such as social support and social learning, to enact behavioral change related to drug use, weight-loss, and type 2 diabetes.^14-17^ Similarly, recent literature illustrated that social network characteristics, such as size, closeness, and density, can also influence a person’s health by shaping the access to information, opportunities, and social norms, thereby enabling or constraining behaviors.^18,19-22^ However, there have been a limited number of studies that have directly addressed or modified social network processes, beyond individual perceptions of social phenomena, to comprehensively address emergent social network influences that have been documented to be important to weight-loss and health behavior change. Hence, this proposed study will focus on implementing a behavioral social-network intervention to promote changes in weight loss behaviors. This study will target key social network processes while also prospectively characterizing the composition, structure, and functions of the networks over time.

## 2.3 Rationale

There are a limited number of studies that directly address or modify social network processes, to comprehensively address emergent social network influences that have been documented to be important to weight-loss and health behavior change. Hence, this pilot randomized controlled trial aims to use evidence-based approaches to promote healthy behavioral changes towards weight-loss, which includes addressing key network level processes among participants and their social network members through individualized coaching sessions, and personalized behavioral recommendations.

## 2.4 Risk/Benefit Assessment

### **2.4.1 Known Potential Risks**

Known potential risks of this study includes the following:

- Discomfort with personal information being discussed
- There may be other potential risks other than listed that we cannot predict

### **2.4.2 Known Potential Benefits**

Known potential benefits of this study include the following:

- Potential weight loss
- Gain knowledge of weight loss techniques and positive lifestyle changes
- Improvements to general health due to improved eating and physical activity habits

### **2.4.3 Assessment of Potential Risks and Benefits**

Participants will disclose personal information about lifestyle habits in communication skills sessions with study staff and a social network member. The participant may feel uncomfortable disclosing this information in front of other individuals. To minimize the risk of discomfort, study staff will limit the information discussed during the session and ensure that the participant verbally and physically confirms (consent) that they are comfortable discussing personal information.

## 2.5 Correlative Studies Background

**Not applicable**

# 3. Study Design

## 3.1 Overall Design

This randomized controlled trial comparing a social-network enhanced lifestyle intervention (intervention group) to an individual-level lifestyle intervention (control group) will be conducted among 132 adult individuals who self-identify as Black or Hispanic with obesity (BMI ≥ 30 kg/m2). The hypothesis being tested is that the multi-component social-network enhanced lifestyle intervention will be feasible, acceptable, and lead to positive change in key social network processes (communal coping, social norms, and affect) that will reduce established interpersonal barriers (social undermining, unhealthy social norms, and interpersonal conflict) to weight-loss. 132 index participants will be recruited and evenly randomized to either the social network intervention group or the control group. Both groups will be followed over 24 weeks (6 months), completing virtual coaching sessions on zoom, along with three in person dietary assessments and weigh-ins. Individuals randomized to the intervention will nominate up to two personal social network members who will participate with the index participants in three virtual communication skills sessions.

[figure not shown]

##

## 3.2 Scientific Rationale for Study Design

Our study is informed by the social cognitive theory (SCT), which posits that individual-level behaviors are shaped by a dynamic interaction between people (personal factors), behavior, and environments. This interaction is demonstrated by the construct called Reciprocal Determinism. Personal factors, environmental factors, and behavior continuously interact through influencing and being influenced by each other. **An intervention must target all three elements to invoke lasting change in behaviors**. The ROBUST intervention will specifically target the: 1) participants' self-efficacy and affective state by teaching them (and their participating network members) how to induce a positive affect and affirmative state using a simple, teachable self-directing script; 2) acquisition of behavioral skills in self-regulation that will enhance adherence to dietary and physical activity goals; and 3) environmental factors of positive reinforcement, social support, weight-related norms and collaborative problem solving (communal coping) by implementing virtual one-on-one lifestyle coaching and communication skills training within the personal network. By intervening and measuring key variables at the individual and interpersonal level, we have married the SCT to Social Network Theory (SNT). SNT elucidates the role of social relationships and social structure in transmitting information, channeling interpersonal influence, and enabling attitudinal or behavioral change.

## 3.3 Justification for Dose

Using the Guidelines (2013) for Managing Overweight and Obesity in Adults as a framework, the number of sessions selected for the intervention and control group is consistent with the principal components of comprehensive lifestyle modification, which include diet, physical activity, and behavior therapy. To lose weight, the guidelines recommend participation for 6 months in high-intensity programs that provide 14 or more counseling sessions with a trained interventionist.^25,26^

## 3.4 End of Study Definition

A participant is considered to have completed the study if he or she has completed all phases of the study including the last visit. The end of the study is defined as completion of the last visit or the completion of the withdrawal procedure.

# 4. Subject Selection

## 4.1 Study Population

Subjects that meet the inclusion criteria will be eligible for participation in this study.

Social network subjects identified by index participants that are willing to be engaged in the study will also be eligible for participation in this study.

## 4.2 Inclusion Criteria Index Participant

1. Black race or Hispanic ethnicity

2. Male or Female 18 years of age or older

3. Calculated BMI > 30kg/m^2^ from objectively measured height and weight by study staff

4. Access & willingness to use program food intake app via home computer or a smartphone

5. Ability to identify at least one adult social network member who will participate in the study

## 4.3 Exclusion Criteria Index Participant

1. Active enrollment in a weight-loss program, use of weight-loss medications, or planning weight-loss surgery

2. Advanced medical illness, dementia, hospitalization, injury, or pregnancy that inhibits regular physical activity

3. Contraindications to exercise based on the Physical Activity Readiness Questionnaire or lack of clearance from a health care provider

4. Unresolved Food insecurity

5. Speaks a language other than English or Spanish

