## 4.6 Strategies for Recruitment and Retention

Recruitment Strategies:

- An estimated 800 Black or Hispanic individuals 18 years of age or older will need to be screened in order to reach the target enrollment of 132 participants.
- The anticipated accrual rate is 8 participants per month (6% of target enrollment)
- Recruitment will take place at four outpatient clinic sites Weill Cornell Internal Medicine Associates, Weill Cornell Urology @ Brooklyn, Weill Cornell Urology @ Upper East Side, and Weill Cornell Primary Care at Lower Manhattan.
- Potential participants will be identified through a TRAC request in EPIC specific to those clinical sites. Study staff will contact the medical provider to verify that the participant is fit to potentially participate in the study and ask their permission to contact the potential participant. Participants will be contacted via phone call, email or regular mail based on their indicated preferences for communication in the electronic health record.
- Recruitment strategies will include mailing potential participants flyers describing the study with the study team contact information.

Retention Strategies:

- - Collection of monthly screening, enrollment, and retention logs
  - Index participants will be compensated $25 for each in person visit
  - Social network participants will be compensated $25 for each completed survey
  - Participants will receive text and call reminders for each scheduled visit

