## 8.2 Participant Discontinuation/Withdrawal from the Study

Participants are free to withdraw from participation in the study at any time upon request.

An investigator may discontinue or withdraw a participant from the study for the following reasons:

- Pregnancy
- Significant study intervention non-compliance
- If any clinical adverse event (AE), laboratory abnormality, or other medical condition or situation occurs such that continued participation in the study would not be in the best interest of the participant
- Disease progression which requires discontinuation of the study intervention
- If the participant meets an exclusion criterion (either newly developed or not previously recognized) that precludes further study participation
- Participant lost to follow-up after several attempts to contact subject to schedule study visit.

The reason for participant discontinuation or withdrawal from the study will be recorded on the Withdrawal Case Report Form (CRF). Subjects who sign the informed consent form and are randomized but do not receive the study intervention will be replaced. Subjects who sign the informed consent form, and are randomized and receive the study intervention, and subsequently withdraw, or are withdrawn or discontinued from the study, will not be replaced.

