### **13.1.5 Reporting Events to Participants**

**Not applicable**

### **13.1.6 Events of Special Interest**

**Not applicable**

### **13.1.7 Reporting of Pregnancy**

Participants must report any instance of pregnancy, in which they will be removed from the study.

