## 13.4 Time Period and Frequency for Event Assessment and Follow Up

The occurrence of an adverse event (AE) or serious adverse event (SAE) may come to the attention of study personnel during study visits and interviews of a study participant presenting for medical care, or upon review by a study monitor.

All AEs including local and systemic reactions not meeting the criteria for SAEs will be captured on the appropriate case report form (CRF). Information to be collected includes event description, time of onset, clinician’s assessment of severity, relationship to study product (assessed only by those with the training and authority to make a diagnosis), and time of resolution/stabilization of the event. All AEs occurring while on study must be documented appropriately regardless of relationship. All AEs will be followed to adequate resolution.

Any medical condition that is present at the time that the participant is screened will be considered as baseline and not reported as an AE. However, if the study participant’s condition deteriorates at any time during the study, it will be recorded as an AE.

Changes in the severity of an AE will be documented to allow an assessment of the duration of the event at each level of severity to be performed. AEs characterized as intermittent require documentation of onset and duration of each episode.

Study team members will record all reportable events with start dates occurring any time after informed consent is obtained until 7 (for non-serious AEs) or 30 days (for SAEs) after the last day of study participation. At each study visit, the investigator will inquire about the occurrence of AE/SAEs since the last visit. Events will be followed for outcome information until resolution or stabilization.

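### Pregnancy bars entry only when it limits physical activity (4.3), yet any pregnancy requires removal (13.1.7), so an active pregnant person can be randomised and must then be withdrawn

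*Protocol*

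**What the plan says.** **Entry.** Section 4.3, item 2, excludes an index participant for "Advanced medical illness, dementia, hospitalization, injury, or pregnancy that inhibits regular physical activity". None of the five inclusion criteria in 4.2 mentions pregnancy. Item 3 of 4.3 excludes for "Contraindications to exercise based on the Physical Activity Readiness Questionnaire or lack of clearance from a health care provider". Before anyone is approached, the recruitment section provides that "Study staff will contact the medical provider to verify that the participant is fit to potentially participate in the study". Neither of these two checks names pregnancy.

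**On study.** Section 13.1.7 reads: "Participants must report any instance of pregnancy, in which they will be removed from the study". Section 8.2 lists pregnancy under the sentence "An investigator may discontinue or withdraw a participant from the study for the following reasons". Section 7.9, which lists the events that end a subject's follow-up, does not include pregnancy.

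**Replacement.** Section 8.2 distinguishes two cases: "Subjects who sign the informed consent form and are randomized but do not receive the study intervention will be replaced", whereas those who have received the intervention "and subsequently withdraw, or are withdrawn or discontinued from the study, will not be replaced".

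**Network members.** Section 4.5 excludes social network members only on language, so they have no pregnancy criterion.

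**The concern.** The entry rule and the removal rule use different tests for the same condition. The entry rule asks whether the pregnancy restricts exercise. The removal rule asks only whether there is a pregnancy. Anyone who falls between the two can be admitted under one section and must be taken out under another.

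The entry test also looks at only half of the programme. Both arms are behavioural weight-loss interventions (section 1), and a fall in caloric intake is a secondary endpoint (1.2.5). Being able to exercise says nothing about whether the dietary and weight-loss aims suit a pregnant participant.

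Two things are at stake. One is participant protection: a person whom the protocol would remove can first be randomised to the programme. The other is an avoidable loss after randomisation, which a screening question would have turned into an ordinary screen failure.

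**Working it through.** There is no figure in the plan to reproduce. The check is mainly a comparison of text, followed by a small calculation of size.

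**Step 1. Can the qualifier in 4.3, item 2, be read so that it leaves pregnancy out?** The clause about inhibiting physical activity comes directly after pregnancy, the last noun in the list. Whether it governs only that noun or the whole list, it governs pregnancy. On neither reading is pregnancy an unconditional exclusion.

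**Step 2. Does another written criterion close the gap?** Take an index candidate who is pregnant, active, without an exercise contraindication on the questionnaire, and cleared by her provider.

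| Rule | Result for this candidate |
| --- | --- |
| 4.2, five inclusion criteria | can meet all; pregnancy not mentioned |
| 4.3, item 2 | not excluded, because activity is not inhibited |
| 4.3, item 3 | not excluded, by assumption |
| Provider check before contact | passed, by assumption; pregnancy not named |
| 6.1.1, screening visit | lists informed consent only |
| 13.1.7 | must be removed |

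She meets the written entry criteria and then falls under the removal rule. The clause in 8.2 on withdrawing someone found to meet an exclusion criterion does not reach her, because she does not meet 4.3, item 2.

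**Step 3. What happens to her place?** Under 8.2 it is refilled if she is removed after randomisation but before receiving the intervention. It is not refilled if she has already received it. Section 12.4.1 defines retention as completion of the 24-week assessment among those with a baseline assessment, so without a week-24 assessment she counts as a loss.

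**Step 4. Size.** The third primary endpoint asks for at least 85% of participants and their network members to complete the final assessment. The protocol does not say whether this is pooled or calculated by group, so three denominators from section 1 are shown.

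| Denominator | Completers needed (0.85 × n, rounded up) | Losses allowed | Cost of one removal (1/n) |
| --- | --- | --- | --- |
| 264, everyone enrolled | 224.4 → 225 | 39 | 0.38 points |
| 132, all index participants | 112.2 → 113 | 19 | 0.76 points |
| 66, intervention index participants | 56.1 → 57 | 9 | 1.52 points |

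With zero, one or two people affected, the most this uses is 2 of the 9 losses allowed on the smallest denominator. Power is not a concern either: the stopping-rules table in section 15 still shows 96% power at 30% dropout.

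**The case against.** The best defence is that the outcome is already covered. Recruitment goes through a provider who verifies fitness and gives permission for contact, lack of clearance is an exclusion, and 13.1.7 removes anyone whose pregnancy becomes known. The protocol describes the trial as minimal risk, and walking is the recommended activity. All of this is fair, and it is why the expected number is small. It does not close the gap in writing: both checks are made case by case without naming pregnancy, and 13.1.7 acts only after the person has been admitted.

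Four stronger readings are tempting, and the documents do not support them.

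- *Section 8.2 adds a third, conflicting rule by making withdrawal discretionary.* The same list of permitted reasons includes loss to follow-up, which 8.3 makes a definite withdrawal. The list gives the investigator authority, and a specific rule elsewhere can govern. Section 13.1.7 is that specific rule for pregnancy. The wording of 8.2 is worth aligning, but staff are not left without a rule.
- *A participant pregnant at entry might stay in while one who conceives later is removed.* This needs the sentence in 13.4, "Any medical condition that is present at the time that the participant is screened will be considered as baseline and not reported as an AE", to limit 13.1.7. That sentence is about recording adverse events, and 13.1.7 does not restrict itself to conception during the study.
- *The removal rule shows that the sponsor judges the programme unsafe in pregnancy.* Section 13.1.7 gives no reason. Protecting the 24-week weight outcome from gestational change would explain it equally well.
- *The completion endpoint is threatened.* It is not, on any of the three denominators.

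It is also true that the protocol does not say which rule was intended, so narrowing 13.1.7 to match 4.3 would restore consistency too. That would leave pregnant participants in a calorie-reduction programme on the strength of exercise capacity alone, and so is the weaker choice.

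**Conclusion.** The point holds as an inconsistency between 4.3, item 2, and 13.1.7. Followed as written, the entry rule admits a person whom the removal rule takes out, and if she has received the intervention her place is not refilled. It is a matter of participant protection and rule consistency and has almost no statistical weight: one loss is about 0.4, 0.8 or 1.5 percentage points of completion, depending on the denominator.

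The conclusion rests on three assumptions. Provider clearance and the exercise questionnaire do not by themselves stop every pregnant applicant; the questionnaire's items are not in the document, so this cannot be checked. Section 13.1.7 means any pregnancy, as its words say. Removal from the study means that no week-24 assessment is obtained; section 7.10 provides for follow-up after removal but does not say which assessments it includes. The number of people affected is unknown and may be zero.

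**What to change.** 1. In 4.3, item 2, take pregnancy out, so that the item ends with injury and the activity qualifier applies to what remains.
2. Add a separate exclusion to 4.3 for index participants: *Current pregnancy*, with no qualifier.
3. Add one self-report question on current pregnancy at screening, before randomisation.
4. In 13.1.7, state that the removal rule applies to index participants. The recruitment section also calls network members participants. They have no pregnancy exclusion, and their coaching is three communication sessions. Removing them would hurt the engagement and completion endpoints for no evident gain.
5. Align 8.2 and 7.9 with 13.1.7: state in 8.2 that an index participant who becomes pregnant will be removed, and add pregnancy to the list in 7.9.

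The cost is an amendment to the wording of four sections and one screening question. The downside is possibly one or two fewer eligible people. Sample size and analysis do not change.
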